#### Parenting stress

The Nosi-K [48] is a Dutch translation and short version of the Parenting Stress Index [49]. This instrument screens for stress related to the caregiver-child relationship and consists of 25 items, rated on a six point scale (1 = totally disagree, 2 = disagree, 3 = somewhat disagree, 4 = somewhat agree, 5 = agree, 6 = totally agree). The complete Nosi questionnaire has Cronbach’s alpha between 0.63 and 0.97 and moderate concurrent, discriminant and criterion validity [48,50].

#### Quality of life

The kiddy-KINDL [51] is a questionnaire to measure health-related quality of life in young children (4 to 7 years). Kiddy-KINDL parent version consists of 24 items, over six dimensions: physical well-being, emotional well-being, self-esteem, family, friend and everyday functioning. Items are rated on a five point scale (1 = never, 2 = rarely, 3 = sometimes, 4 = often, 5 = all the time). The KINDL has good psychometric qualities [51]. We used a Dutch translation of the kiddy-KINDL.

### Sample size calculation

Sample size is calculated based on the DAI (see Measures). The DAI is a dichotomous measure reflecting symptoms of disturbed attachment (1 = not or somewhat present, 2 = definitely present). From cross-sectional data it is known that the prevalence of symptoms of disturbed attachment in comparable populations is approximately 40% [39]. Based on unpublished pilot data, which also suggested 40% of participants would be symptomatic at any time-point in the TAU intervention, we expect that in the present randomized controlled trial (RCT), a 40% level of symptomatic individuals will be maintained until the end of the TAU. Based on Fisher and Kim’s study [24], which reported increased secure attachment behavior (behavior that is incompatible with disturbed attachment) after MTFC-P, we expect a decline of disturbed attachment over the course of the MTFC-P. The aim is to reduce the proportion of children with symptoms of disturbed attachment to 5% at the end of MTFC-P. Including 34 children in both conditions can statistically reveal a difference between conditions with 90% power, using Fisher's exact test with a 0.05 two-sided significance level for analysis. The study was initially planned as a ‘normal’ pre-randomization trial. However, we observed low recruitment of participants because children arrive in a crisis situation and obtaining consent from biological parents was problematic (see below, Randomization). We therefore changed to a pre-randomization with single consent method to allow the birth parents enough time to decide on their participation. Parents of children randomized to MTFC-P who refused consent received TAU after randomization. We expected a 10% cross-over rate. This cross-over rate reduces the efficiency of the trial by 19% and requires a 20% addition to the sample size [52]. We therefore augmented the planned sample size from 34 to 40 per treatment arm (under 90% power) to counter the dilution effects by the cross-overs in the intention-to-treat analysis and to diminish the type II error probability.

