
Previous studies in the US have shown that, relative to children in regular foster care, children in MTFC had fewer placement failures [22], improved HPA axis functioning [23], increased secure attachment behavior and less resistant behavior [24]. Although MTFC-P is quite successful in the US and transportability of the MTFC model for older children has been shown in a Swedish context [25], the efficacy of the preschool version has not been replicated in other countries where implementation challenges and cultural differences may play a role. Outside the US, in the Netherlands, only a small pilot study was conducted, preliminary to this study. Early findings suggested less problem behavior in the MTFC-P intervention [26].

This protocol is for a study intending to examine whether US findings regarding MTFC-P also apply for children in foster care in the Netherlands. The study also aims to extend on previous studies by examining the effects of MTFC-P on post-traumatic stress symptomatology, symptoms of attachment disorder and quality of life. With the present study, we compare the effects of MTFC-P with a treatment as usual (TAU) for foster children at risk for placement breakdown. We hypothesize that MTFC-P is more effective than TAU for young foster children with emotional and behavioral disorders. Effectiveness is measured in terms of decreased problem behavior; fewer symptoms of disturbed attachment; fewer severe post-traumatic stress symptoms; improved quality of life; recovery of HPA-axis functioning, indicated by recovery of atypical cortisol activity; and less parental stress. We expect that, relative to control children, at the end of the treatment children in the MTFC-P group will show less maladaptive responses of the ANS, indicated by heart rate, respiratory sinus arrhythmia and pre-ejection period, to separation and reunion with caregivers and strangers.

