### Primary objectives

#### Problem behavior

The Child Behavioral Checklist for ages 1.5 to 5 (CBCL 1.5-5 [29]) and 6 to 18 (CBCL 6–18 [30]) assesses the internalizing and externalizing behaviors of children. The CBCL is completed by foster parents and consists of hundred (ages 1.5-5), respectively 113 (ages 6–18) items. Items are rated on a 3-point scale (*0 = not at all true, 1 = somewhat true, 2 = very true*). A Dutch translation of the CBCL is used. Prior studies in Dutch populations revealed satisfactory reliability and validity of the CBCL 1.5-5 and 6–18 [31,32]. Preliminary analyses based on data from the present study revealed good internal consistency with alphas >0.80 for all scales except for internalizing problems (alpha = 0.60).

The Teacher Report Form for ages 1.5 to 5 (TRF 1.5-5 [29]) and 6 to 18 (TRF 6–18 [30]) assesses children’s school functioning and behavioral problems. The TRF is completed by foster parents and consists of hundred (ages 1.5-5), respectively 113 (ages 6–18) items. Items are rated on a 3-point scale (*0 = not at all true, 1 = somewhat true, 2 = very true*). Depending on the age of study children, daycare providers or teachers complete this questionnaire. Preliminary analyses based on data from the present study revealed good internal consistency with alphas >0.80 for all scales except for internalizing problems (alpha = 0.44) and externalizing problems (alpha = 0.58). A Dutch translation of the TRF is used. Psychometric properties have been found to be adequate in Dutch populations [33].

The Strengths and Difficulties Questionnaire (SDQ [34]) is a behavioral screening instrument, completed by (foster) parents. This questionnaire consists of 25 items, rated on a three point scale (0 = not true, 1 = somewhat true, 2 = very true) testing children’s psychological attribution to five subscales and one total scale (alphas given in parentheses): emotional problems (0.65), conduct problems (0.68), hyperactivity (0.77), peer relations (0.57), prosocial behavior (0.73) and total difficulties (0.67). Alphas were based on preliminary data from the present study. We use a Dutch translated version of the SDQ. Reliability and validity of the SDQ-parent report in a Dutch sample have been found to be satisfactory [35].

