The Parent Daily Report (PDR [36]) is a telephone interview with foster carers and is conducted daily during weekdays. It assesses the occurrence of 38 problem behaviors (for example, cruelty to animals, arguing) within the past 24 hours, which are scored on a two-point scale (0 = not occurred, 1 = occurred at least once). The PDR has previously been used as a measure for treatment outcomes; psychometric properties have been found to be adequate [37]. The PDR is translated into Dutch.

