A second limitation to our RCT is the lack of an adequate baseline measure. Because children are new in the foster family at the start of the intervention, we decided to postpone the first assessment. A new placement is often accompanied by a temporary increase or decrease in problems, and foster carers and children have just met. Adhering to a randomized trial will minimize baseline differences between children in the two conditions. A third limitation is that foster parent’s perception of children’s behavior is one of the primary focuses of the treatment, but also a primary objective of the present study. We attempt to limit the effect of reactive measures by the inclusion of teachers’ perceptions of children’s behavior. In addition, we inserted the Strange Situation Procedure. Although this observation of attachment is only post-treatment, we expect that the random allocation will diminish selection bias. Other alternatives have been considered, such as observational measures of children’s behavior, but their benefits are not expected to compensate for the extra burden they would place on participants. If we are able to meet the challenges and include sufficient participants, we will generate knowledge about the effectiveness of an intensive behavioral focused program, developed to gain stability of placement for young foster children.

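### Six instruments share the primary tier, but only the DAI is sized and given a significance level, and no confirmatory test or decision rule is named

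*Protocol article*

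**What the plan says.** The Measures part of the Methods has a tier headed "Primary objectives", in the plural. Six instruments stand in it before the secondary tier begins:

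- CBCL, which "assesses the internalizing and externalizing behaviors of children"
- TRF, which "assesses children’s school functioning and behavioral problems"
- SDQ: "The Strengths and Difficulties Questionnaire (SDQ [34]) is a behavioral screening instrument"
- PDR: "The Parent Daily Report (PDR [36]) is a telephone interview with foster carers"
- DAI, under Attachment, with three subscales
- Strange Situation Procedure, under Attachment

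The Discussion confirms that problem behavior is meant to rank as primary. It describes the foster parent's perception of the child's behavior as "one of the primary focuses of the treatment, but also a primary objective of the present study".

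The Sample size calculation opens with "Sample size is calculated based on the DAI (see Measures"). It compares 40% symptomatic under TAU with 5% under MTFC-P by Fisher's exact test at two-sided 0.05 with 90% power. This gives 34 per arm, raised to 40 for an expected 10% cross-over. No other instrument is sized or given a significance level.

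The Background states one hypothesis, that MTFC-P is more effective than TAU, and then a list of domains: "Effectiveness is measured in terms of decreased problem behavior; fewer symptoms of disturbed attachment; fewer severe post-traumatic stress symptoms", followed by further outcomes. It does not say whether any, all or an ordered set of these must succeed. Planned statistical analyses assigns tests by type of data and gives 95% confidence intervals. It uses the word primary only for the intention-to-treat analyses, not for an outcome.

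**The concern.** The test that was sized is nowhere identified as the confirmatory one, and five unsized instruments hold the same rank. The stated 5% error and 90% power therefore describe one of at least six primary comparisons. A reader of the results could not tell whether a significant CBCL or Strange Situation result is confirmatory or one chance finding among several. Nor could the reader tell how to read a null DAI next to a positive questionnaire.

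Timing adds to this. Under Status of the trial, inclusion is still in progress, and reliability figures from the trial's own data are already reported. A primary test chosen after the arms have been compared would carry little weight.

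**Working it through.** **1. The plan's own figure.** Inputs from Sample size calculation: rates 0.40 and 0.05, two-sided 0.05, power 0.90.

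- Mean rate (0.40 + 0.05)/2 = 0.225; difference 0.35.
- Uncorrected n = [1.96 × √(2 × 0.225 × 0.775) + 1.2816 × √(0.40 × 0.60 + 0.05 × 0.95)]² / 0.35² = 27.8, so 28 per arm.
- With the continuity correction: 34 per arm, which matches the article. Full enumeration of Fisher's exact test gives 93.7% power at 34, so 34 is slightly conservative.
- Cross-over: 1 − 0.9² = 19%; 34 × 1.20 = 40.8 and 34/0.81 = 42.0, against the planned 40.
- Diluted MTFC-P rate: 0.9 × 0.05 + 0.1 × 0.40 = 0.085. Exact Fisher power at 40 per arm is then 90.0%.

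The sizing is sound for the DAI as a single test.

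**2. What six primary tests would do to the error rate.** The article gives no family-wise figure. This step needs three assumptions that it does not state: one test per instrument, each at two-sided 0.05; any one significant result counts as success; and a common correlation between test statistics. Under no effect and independence:

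- either direction: 1 − 0.95⁶ = 26.5%
- favouring MTFC-P only: 1 − 0.975⁶ = 14.1%

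With correlation, from 1,000,000 simulated sets of six equicorrelated normal statistics:

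| Assumed correlation | Any false positive, either direction | False result favouring MTFC-P |
|---|---|---|
| 0 | 26.5% | 14.1% |
| 0.3 | 24.1% | 12.2% |
| 0.5 | 20.7% | 10.4% |
| 0.7 | 16.5% | 8.2% |

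The single-test values are 5% and 2.5%. Fisher's exact test is conservative: its actual size is 3.0% at 40 per arm with a 40% rate. Using that for the DAI lowers the independent either-direction figure from 26.5% to 24.9%.

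**3. Sensitivity to the count.** With one test per domain (problem behavior, attachment), the figures fall to 1 − 0.95² = 9.75% in either direction and 1 − 0.975² = 4.9% favouring MTFC-P. If the scales were tested separately (two each for CBCL and TRF, three for DAI, one each for SDQ, PDR and Strange Situation), there would be ten tests, and the favourable figure under independence would be 1 − 0.975¹⁰ = 22.4%.

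**4. Power under each remedy, 40 per arm, exact Fisher test for the DAI.**

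- DAI as sole primary at 0.05: 97.3% without cross-over, 90.0% with 10% cross-over.
- DAI at the Bonferroni level over six, 0.05/6 = 0.00833: 87.9% without cross-over, 71.0% with it. About 90% with cross-over would need slightly more than 56 per arm (89.4% at 56).

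**The case against.** The strongest reply is that a multiplicity rule is commonly left to an analysis plan, and that plan is not shown here. That stands as far as it goes: the missing adjustment procedure alone would not be a finding. It does not cover the choice of primary outcome, which belongs in a protocol. This article makes that choice by placing six instruments in the tier and powering one.

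Several stronger readings are tempting, and the text does not support them:

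- A reader might infer that all six are to be tested at an unadjusted 0.05. That level is stated only for the DAI.
- A reader might infer that success on any one instrument is enough. The Background only lists domains. If all had to succeed, there would be no inflation.
- A reader might quote the 21-26% as the chance of falsely declaring MTFC-P effective. Those figures include results favouring TAU; the directional figures are about half as large.
- A reader might add inflation for the six time-points. Planned statistical analyses provides for repeated-measures mixed models, which take the time-points together, and Data collection schedules the DAI only at T(2) and T(4).
- A reader might take the sample size to be wrong. It reproduces.

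It is also fair that CBCL, SDQ and PDR are all foster-carer reports of the same behavior, so correlations may be high and the lower rows of the table may be nearer the truth. Finally, demoting problem behavior is more than an edit of wording. It is listed first among the primary objectives and is the stated target of MTFC-P, and recruitment has run since mid-2009.

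**Conclusion.** The point holds in limited form. The article ranks six instruments as primary, sizes and sets a significance level for one, and states no single primary test, decision rule or multiplicity control. This should be corrected.

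The possible inflation is conditional. With one test per instrument at two-sided 0.05 and any success counting, a false result favouring MTFC-P has a chance of about 14% under independence, 10% at correlation 0.5 and 8% at 0.7. In either direction the figures are about 26%, 21% and 16-17%. The testing level for the other five instruments, the any-one rule and the correlations are assumptions. Even the lowest of these six-test figures is over three times the corresponding single-test value.

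**What to change.** Before any between-arm comparison, name one confirmatory test: DAI symptomatic (a score of 2 on any item) versus not, at T(4), by Fisher's exact test at two-sided 0.05, intention to treat. This is the comparison that was sized. It keeps 40 per arm and lets the stated error and power apply as written. Report CBCL, TRF, SDQ, PDR, Strange Situation and the DAI subscales as secondary, with estimates and intervals and no confirmatory claim.

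If problem behavior must stay confirmatory, state which scale and time-point represent each instrument, adopt a Holm or similar procedure, and restate the DAI's power. The Bonferroni figure over six, about 71% with 10% cross-over, is a floor for Holm, which rejects whatever Bonferroni rejects.

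Cost: the first option needs a short dated amendment and no extra children, but problem behavior loses confirmatory status. The second keeps that status at the price of DAI power or a larger trial.

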### Procedure

#### Recruitment

Eligible children are recruited from the department of Treatment Foster Care at De Bascule, Academic Center for Child and Adolescent Psychiatry (Amsterdam, Netherlands). Children’s legal authorities and foster carers receive information about the study. After approximately one week, a researcher contacts them and asks if all the information is understood. When children’s legal authorities or foster carers are interested in participation, an appointment is made to sign explicit informed consent.

#### Randomization

Random allocation to either condition is needed to reduce selection bias and to be able to attribute effects to MTFC-P or TAU. However, referral to foster care is often made in crisis and immediate start of care is a prerequisite. The start of foster care is also usually accompanied by resistance or absence of the biological parent (the child’s legal authority) or a vacuum in authority. We expect this brief time interval between referral and start of the intervention, together with inaccessibility of a legal authority, to hamper random allocations. Following conventional randomization, researchers are unable to ensure that the child’s legal authority has retrieved, understood and signed informed consent before the child must be allocated to a treatment [53]. This results in a preliminary loss of participants. A pre-randomization trial, wherein randomization is determined prior to informed consent [54], is implemented as this promotes the inclusion of participants by extending the time period between referral and start of treatment. Researchers then have more time to obtain informed consent, avoiding preliminary dropout [55]. An independent researcher makes a random allocation list, varying per time period. Distribution of assignment to both conditions varies over time periods (approximately every six months), based on available treatment places. This is necessary to guarantee that children receive immediate treatment and are not placed on a wait list. Conditions are disclosed to the treatment team and participants immediately after referral. If legal authorities will not sign informed consent, children receive TAU. The condition is not disclosed to any members of the research team concerned with coding data.

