**Methods:**

This is a randomized controlled trial, wherein we expect to include 80 child-foster carer dyads. Forty dyads will be assigned to Multidimensional Treatment Foster Care for Preschoolers and 40 to treatment as usual, following pre-randomization. Data to be gathered concern problem behavior, symptoms of attachment disorder, post-traumatic stress symptoms, quality of life, hypothalamic-adrenal-pituitary axis functioning, parental stress and autonomic reactivity, to be collected via questionnaires, observations, interviews, saliva and recording at six time-points over 24 months. To compare treatment outcomes, Fisher’s exact tests and repeated measures (mixed models) and independent t-tests will be used. All analyses will be performed following the intention-to-treat principle.

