#### Planned statistical analyses

Analyses are performed using the software package SPSS (Statistical Package for the Social Sciences), version 17.0. Fisher’s exact tests are used for the categorical data, effect sizes are estimated by the relative risks, absolute risks and relative risk reduction. Effect parameters are presented within a 95% confidence interval. The continuous measures are analyzed with repeated measures (mixed models) and independent t-tests. Effect sizes are indicated by partial eta squared and Cohen’s d. Primary analyses are performed following the intention-to-treat principle. However, we will also perform a ‘treatment received’ analysis and a separate comparison of children whose parents refused participation and who received TAU after randomization to MTFC-P. Depending on the amount and type of data missing we will explore possibilities to deal with missing data, but we plan to use mixed models.

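### The allocation ratio changes about every six months, but the planned Fisher's exact and independent t-tests pool over those periods, so a calendar trend could bias the comparison

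*Protocol article*

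**What the plan says.** The Randomization section describes a separate list for each period: "An independent researcher makes a random allocation list, varying per time period". It adds: "Distribution of assignment to both conditions varies over time periods (approximately every six months), based on available treatment places". The reason given is that children must start treatment at once rather than wait. Overall the arms are meant to be equal (Abstract, Methods): "Forty dyads will be assigned to Multidimensional Treatment Foster Care for Preschoolers and 40 to treatment as usual, following pre-randomization".

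Planned statistical analyses then states: "Fisher’s exact tests are used for the categorical data, effect sizes are estimated by the relative risks, absolute risks and relative risk reduction". For the other outcomes: "The continuous measures are analyzed with repeated measures (mixed models) and independent t-tests". The article does not name allocation period as a stratum, a covariate or a sensitivity analysis. Sample size calculation rests on an unstratified Fisher's exact test of the DAI.

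The article also records one change made while the trial was running, after recruitment proved low: "We therefore changed to a pre-randomization with single consent method". Status of the trial says that recruitment began in mid-2009 and was still open when the article appeared in July 2013. That is about four years, or roughly eight six-month periods.

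**The concern.** When the ratio differs between periods, a child's chance of receiving MTFC-P depends on when the child was referred. A pooled two-sample test then partly compares children from periods rich in MTFC-P with children from periods rich in TAU. If the outcome also differs between those periods, part of that difference is credited to treatment. A standard Fisher's test or independent t-test has no place for a period term, so this does not depend on a detail that an analysis plan might add to the same tests.

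Two features of the article make it matter more. The Discussion relies on randomisation to keep the arms alike at the start, and it concedes that there is no adequate baseline measure. An imbalance between periods would therefore be hard to see or correct afterwards. The change of consent method is also a documented reason why the children entering might differ over time. At stake are the DAI comparison on which the trial is sized, the relative and absolute risks promised with it, and every continuous outcome tested by t-test.

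**Working it through.** **1. The plan's own figure.** Inputs from Sample size calculation: TAU 40% ("a 40% level of symptomatic individuals will be maintained until the end of the TAU"), MTFC-P 5%, two-sided 0.05, power 90%.

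- Uncorrected: n = [1.96·√(2 × 0.225 × 0.775) + 1.28·√(0.40 × 0.60 + 0.05 × 0.95)]² / 0.35² ≈ 27.8, so 28.
- Continuity-corrected: (27.8/4)·[1 + √(1 + 4/(27.8 × 0.35))]² ≈ 33.3, so **34 per arm, as stated**. Exact Fisher power at 34 is 93.7%.
- With the stated 10% cross-over, the MTFC-P rate becomes 0.9 × 5% + 0.1 × 40% = 8.5%. At 40 per arm, exact Fisher power for 40% v 8.5% is 90.0%.

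The planned size is thus consistent with the stated 90%, for an unstratified test.

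**2. Bias of the pooled comparison with no treatment effect.** Let period k hold m_k MTFC-P and t_k TAU children with outcome mean p_k in both arms. The pooled difference has expectation Σ(m_k/40 − t_k/40)·p_k. If a share r goes to MTFC-P in the first half and 1 − r in the second, this is (2r − 1) × (first-half mean − second-half mean). It is zero if the ratio is constant or if there is no trend.

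The ratios and trends below are assumptions.

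- *Two blocks of 40, prevalence 30% then 50%.* At 70:30 then 30:70: 0.4 × (−20) = −8 points. At 80:20 then 20:80: 0.6 × (−20) = −12 points.
- *Eight periods of 10, linear drift from 50% to 30%.* The half means are 45.7% and 34.3%, a gap of 11.4 points. At 7:3 then 3:7: 0.4 × 11.4 = 4.6 points. At 8:2 then 2:8: 0.6 × 11.4 = 6.9 points. Alternating 7:3 and 3:7: neighbouring periods differ by 20/7 = 2.9 points, and 0.4 × 2.9 = 1.1 points.

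Size of the pooled Fisher test at nominal 5%, by exact enumeration:

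| Trend | Ratio pattern | False difference (points, absolute) | Fisher size |
|---|---|---|---|
| None | 1:1 | 0 | 3.0% |
| Linear, 20 points | 1:1 | 0 | 2.9% |
| Linear, 20 points | alternating 7:3, 3:7 | 1.1 | 2.9% |
| Linear, 20 points | 6:4 then 4:6 | 2.3 | 3.2% |
| Linear, 20 points | 7:3 then 3:7 | 4.6 | 4.3% |
| Linear, 20 points | 8:2 then 2:8 | 6.9 | 6.2% |
| Step, 20 points | 70:30 then 30:70 | 8 | 7.3% |
| Step, 20 points | 80:20 then 20:80 | 12 | 13.8% |

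Reversing the trend reverses the sign, so either arm may be favoured.

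**3. The t-test, drift of 0.5 SD, by simulation.**

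- Eight periods: the half means differ by 0.5 × 4/7 = 0.286 SD. Bias is 0.11 SD at 7:3 (size 7.6%) and 0.17 SD at 8:2 (size 11.4%).
- Two blocks: bias is 0.4 × 0.5 = 0.20 SD at 70:30 (size about 13%) and 0.6 × 0.5 = 0.30 SD at 80:20 (size about 25%).

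**4. After stratifying by period.** In eight periods of 10, the CMH test without continuity correction had simulated type I error between 4.8% and 5.3% in every drift and ratio scenario tried.

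The price is information. Within-period information is Σ m_k·t_k/10, against 40 × 40/80 = 20 for the pooled comparison:

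| Ratio (reversed halfway) | Σ m_k·t_k/10 | Share of 20 | CMH power | CMH power, continuity-corrected |
|---|---|---|---|---|
| 5:5 | 8 × 2.5 = 20 | 100% | 93% | 89% |
| 6:4 | 8 × 2.4 = 19.2 | 96% | 92% | 87% |
| 7:3 | 8 × 2.1 = 16.8 | 84% | 89% | 82% |
| 8:2 | 8 × 1.6 = 12.8 | 64% | 79% | 67% |

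Power is for 40% v 8.5% at 40 per arm, without drift. An exact stratified test gives about 89%, 85% and 74% at 5:5, 7:3 and 8:2.

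**The case against.** The strongest reply is that the risk is conditional. Bias needs an outcome trend and a ratio that moves with it, and the article reports neither. It does not say that the consent change altered DAI prevalence or behaviour scores, or that it coincided with a change of ratio. A ratio that follows free places may well rise and fall rather than turn once. With eight periods at 7:3 or 3:7 in random order and a linear drift from 50% to 30%, the mean absolute bias was 1.6 points, mean Fisher size was 3.1%, and none of 2,000 orders exceeded 5%. Fisher's test is conservative at this sample size, which absorbs mild drift.

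All of this stands, and it rules out the reading that the trial's comparison is biased as a matter of fact. It does not remove the mismatch. The conservatism protects the test but not the risk estimates reported with it, and the t-test has no such cushion.

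A reader might also infer that the planned mixed models are at fault because no period term is named. The article does not support that: covariates are commonly left to a fuller protocol or analysis plan, and a mixed model can carry period. Nor does it support supposing that some periods offered only one arm, since the text speaks of assignment to both conditions.

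A last objection is that stratifying costs power. That is correct where ratios are strongly unequal, and the cost belongs in the plan.

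**Conclusion.** The point holds as a mismatch between design and analysis, limited to the Fisher's exact and independent t-tests. Children are randomised within periods of differing ratio, and these tests ignore the periods. The resulting bias is possible and its direction unknown.

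For a 20-point prevalence drift and no treatment effect, it ranges from about 1 point with no inflation of type I error to 12 points with a size of 13.8%. The gradual-drift scenarios reversing at 7:3 or 8:2 lie between, at 4.6 to 6.9 points and 4.3% to 6.2%. For the t-test the range is about 8% to 25%, under 0.5 SD drift and ratios of 7:3 or 8:2 reversing halfway. These figures rest on assumed ratios, trends and number of periods. They show what could happen, not what did.

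**What to change.** - Record the allocation period and its MTFC-P:TAU ratio for every child, and report the ratios by period.
- Replace the pooled Fisher's test of the DAI with a CMH test stratified by period. Report a Mantel-Haenszel risk difference, and a relative risk where the tables are not too sparse: 5% of 40 is only two expected MTFC-P events spread over about eight strata.
- Replace the independent t-tests with a linear model that has period as a fixed factor, and carry the same factor in the mixed models.
- Merge adjacent periods only where the ratio was the same.
- Recheck and restate the 90% power against the ratios actually used.

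The period can be recovered from the allocation lists, so no new data are needed. The article reports recruitment still open, so the change could be fixed before the final analysis. The cost is small when ratios stay near 1:1 and material at about 8:2. It is larger still if a continuity-corrected or exact stratified test is chosen, so the version of the test should be named in advance.
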